#### Statistical analyses

Preliminary analyses will include graphics/plots, and descriptive statistics. We will compute frequencies and proportions for retention and baseline characteristics, and use t-tests and chi-squared tests to evaluate differences. Alpha will be set to .05, and adjusted for multiple comparisons. Missing values will be handled with appropriate methods (Little & Rubin 2002). Outcome analyses will be conducted with (a) an intent-to-treat (ITT) approach, in which participants with missing data are assigned the status of smoker, and (b) a “per protocol” approach, which will include participants who complete all aspects of the study; (orientation, ≥ four intervention sessions, and all follow-ups). Within-time logistic regressions will determine the odds of abstinence at each assessment, comparing CS-CBT to control. Generalized linear mixed modeling (GLMMs) will examine between-group cessation rates over time, including main effects and interactions, and accounting for nesting within groups. A pattern-mixture analysis will examine whether intervention effects differ according to patterns of missing data (e.g., those who complete only one follow-up). Hierarchical logistic regression will be conducted to explore ethno-cultural predictors of cessation.

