### Measures

#### Baseline

Measures include demographics, smoking history, and nicotine dependence (Heatherton et al. 1991) (Table 2). We also assess perceived stress (Cohen et al. 1983), depressive symptoms (Radloff 1997), and decision making. Particularly relevant for African American smokers, we include assessments of acculturation (Klonoff & Landrine 1999), ethnic identity (Davis et al. 2010), expectancies for culturally specific interventions, and perceived ethnic discrimination (Landrine et al. 2006). We also record height and weight. Participants also complete an “In Case I Move Form” as a method of tracking participants via relatives or friends.

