**Table 2 Tab2:** **Constructs and measures**

Assessment points						
Measure	Baseline	Intra-treatment	End-of-counseling	3-month follow-up	6-month follow-up	12-month follow-up
Attendance	✓	✓	✓	✓	✓	✓
Demographics	✓					
Smoking history	✓					
Nicotine dependence	✓					
Height	✓					
Weight	✓	✓	✓	✓	✓	✓
Perceived stress	✓		✓			
Depressive symptoms	✓		✓			
Acculturation	✓					
Ethnic Identity	✓					
Expectancies for culturally specific Interventions	✓					
Decision making	✓					
Perceived ethnic discrimination	✓					
Nicotine withdrawal		✓	✓			
Smoking urges		✓	✓			
TNP use		✓	✓			
Intervention ratings			✓			
Time-line follow-back (smoking pattern)			✓	✓	✓	✓
Therapist satisfaction			✓			
Carbon monoxide	✓	✓	✓	✓	✓	✓
Cotinine*	✓			✓	✓	✓

Note: *At baseline, saliva for cotinine is collected from all participants. Cotinine samples are not collected at the EOC because participants are still using nicotine replacement. At follow-ups, saliva for cotinine is collected from self-reported abstainers only.

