### Data analyses

#### Sample size and power

Sample size was determined based on Webb et al. (2010) and the formula provided in (Diggle et al. 2002) (p. 31). Webb et al. 2010 found that 51% of participants who received standard CBT reported 7-day ppa at the EOC, and about a 20% relapse rate at 3-months and 6-months. In the CS-CBT pilot study, we found 75% 7-day ppa at the EOC. Assuming a 23% reduction at 3-months, four assessments, with a within-subjects correlation of .60, 65 participants per group will yield power = .80% with a two-sided significance level of 5%. We conservatively anticipated 30% 7-day ppa at 12-months in the CS-CBT condition, and 14% in the control condition. To examine acculturation and ethnic identity as moderators controlling for covariates (e.g., group, sociodemographic factors, etc.), the planned regression analyses require a sample of 124. Thus, the final N is 150 (completing all assessments).

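### The arm comparisons name no baseline covariate, and baseline characteristics are to be significance-tested; prespecified adjustment for nicotine dependence and cotinine would be a small, cheap improvement

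*Protocol article*

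**What the plan says.** In the protocol article, the Statistical analyses section opens with preliminary work: frequencies and proportions for retention and for baseline characteristics, after which the team will "use t-tests and chi-squared tests to evaluate differences". The effect analyses follow. "Within-time logistic regressions will determine the odds of abstinence at each assessment, comparing CS-CBT to control". The generalized linear mixed model is described by its terms: between-group rates over time, main effects and interactions, and nesting within therapy groups. Neither description names a baseline covariate, and neither states that the analysis is unadjusted.

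Covariate control is mentioned only under Sample size and power, for the regressions on acculturation and ethnic identity as moderators.

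The candidate covariates are already in the data. Under Baseline: "Measures include demographics, smoking history, and nicotine dependence". In the note to Table 2: "At baseline, saliva for cotinine is collected from all participants". The Randomization section describes 1:1 allocation in blocks of 50 and names no stratification factor.

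**The concern.** A significance test on a baseline variable asks whether the observed difference is larger than chance would usually give. It does not ask whether the difference is large enough, in a variable prognostic enough, to move the treatment estimate. A non-significant imbalance in a strong predictor can matter, and a significant one in an irrelevant variable does not.

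With no stratification described, balance on dependence and cotinine is left to chance. If either predicts abstinence, a chance imbalance stays in an unadjusted estimate, and a logistic comparison that omits a prognostic variable has somewhat less power than one that includes it. At stake are a few points of power and protection against an unlucky allocation. The validity of the primary comparison is not at stake.

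**Working it through.** **1. The plan's own figure.** Sample size and power states that "65 participants per group will yield power = .80" (printed with a stray percent sign) "with a two-sided significance level of 5" percent, four assessments and a within-subject correlation of 0.60. The repeated-binary calculation multiplies the two-proportion sample size by (1 + (m − 1)ρ)/m = (1 + 3 × 0.6)/4 = 0.70. Per group it gives:

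- 44 for 75% vs 51%. The inputs are "In the CS-CBT pilot study, we found 75% 7-day ppa at the EOC" and "51% of participants who received standard CBT reported 7-day ppa at the EOC".
- 95 at 3 months if the stated falls of 23% and 20% are relative (57.75% vs 40.8%), or 60 if they are absolute (52% vs 31%).
- 73 for 30% vs 14% at 12 months.

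None of these is 65. A single-time-point test needs 63 for 75% vs 51%, and 65 for 52% vs 28% (23 points off both arms), but neither uses the four assessments or the correlation. The 65 is therefore not reproduced from its stated inputs. That is a separate matter, and nothing below depends on it.

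**2. What a baseline test would let through.** Inputs: 75 per arm (half of the final N of 150) and the 12-month rates of 30% vs 14%.

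- Standardised difference that just reaches p = 0.05: 1.96 × √(2/75) = 0.32 SD. Anything smaller would pass as balanced.
- Planned effect: ln(0.30/0.70) − ln(0.14/0.86) = −0.847 + 1.815 = 0.968.
- Approximate shift in the log odds ratio from that imbalance: |ln(OR per SD)| × 0.32.

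| Assumed OR per SD | Shift | Share of 0.968 |
|---|---|---|
| 0.8 | 0.223 × 0.32 = 0.07 | 7% |
| 0.6 | 0.511 × 0.32 = 0.16 | 17% |
| 0.5 | 0.693 × 0.32 = 0.22 | 23% |

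These are single unlucky allocations at the edge of significance. Averaged over randomisation the shift is zero.

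**3. Power with and without adjustment.** Simulated logistic regressions at one time point, without clustering: marginal rates fixed at 30% and 14%, one standard-normal covariate, Wald test of arm. The covariate strength is assumed.

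- 75 per arm: unadjusted power is about 66%. The gain is about 0, 1, 3 and 5 points at OR 0.8, 0.6, 0.5 and 0.4 per SD.
- 123 per arm (247/2, rounded down): the gain is 0 to 3 points over the same range.

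The mechanism is visible at 123 per arm in a separate run of 2,000 trials. An OR of 2.0 is the same strength as 0.5.

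| OR per SD | Log OR, unadjusted → adjusted | SE | Power |
|---|---|---|---|
| 1.3 | 0.985 → 1.001 | 0.331 → 0.335 | 86.4% → 86.6% |
| 1.5 | 0.998 → 1.032 | 0.332 → 0.338 | 86.0% → 87.6% |
| 2.0 | 0.983 → 1.065 | 0.331 → 0.347 | 86.4% → 89.0% |

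The standard error rises. Power improves because the log odds ratio rises faster: in the last row the ratio goes from 0.983/0.331 = 2.97 to 1.065/0.347 = 3.07. At 75 per arm and OR 0.5 the standard error likewise goes from 0.429 to 0.451.

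**4. Risk-difference scale.** Here adjustment does improve precision. Relative efficiency is p₁q₁ + p₀q₀ (q = 1 − p) divided by E[m₁(1 − m₁)] + E[m₀(1 − m₀)] + Var(m₁ − m₀)/2, where m₁ and m₀ are the covariate-specific abstinence probabilities in the two arms. For OR 1.3, 1.5 and 2.0 per SD it is 1.01, 1.03 and 1.08 at 30% vs 14%, and 1.015, 1.035 and 1.10 at 75% vs 51%.

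**The case against.** The article is a condensed account, and a covariate list is often left to the full protocol or analysis plan, which are not shown. A reader might infer that the plan ignores baseline prognosis, that the tests are used instead of adjustment, or that they will choose the covariates. The text supports none of these. The tests are called preliminary, their sentence also covers retention (where testing is reasonable), and nothing links them to the outcome models. An unadjusted comparison of randomised arms is a valid estimate of the marginal effect. All of that stands.

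A reader might also say that the plan gives up precision. For the planned odds ratio this is wrong, since the standard error does not fall on adjustment. Nor do the documents state that dependence or cotinine predicts abstinence in this population; if they do not, the gain is nil. The simulations cover one time point without therapy-group clustering, so they indicate the size for the mixed model without measuring it.

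There is one argument for looking at balance closely. Assignment is tentative until orientation and consent, and orientation differs by arm, so differences among those enrolled need not be pure chance. A descriptive comparison by arm shows this as well as p-values would.

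What survives is narrower. The article does describe the effect models by their terms, and it does plan tests on baseline characteristics. A better method is available with variables already in hand.

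**Conclusion.** The point holds as a minor improvement. As described, both arm comparisons carry no named baseline covariate, and the planned baseline tests are a poor guide to whether an imbalance matters. Nothing is stated wrongly, and the primary comparison is not invalid.

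At the documented 14% vs 30%, the expected power gain is about 0 to 5 points with 75 per arm and 0 to 3 points with 123 per arm, for an assumed covariate odds ratio of 0.8 to 0.4 per SD. A gain near the top of the range needs a very strong covariate. With a weak one, adjustment gains nothing in power and does no material harm. The further benefit is protection against an unlucky allocation, which a non-significant baseline test does not give.

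**What to change.** - Prespecify baseline nicotine dependence score and log baseline cotinine as fixed covariates in the within-time logistic regressions and in the mixed model, whatever their observed balance.
- Present baseline characteristics descriptively by arm without p-values, and state that covariates will not be chosen by baseline tests. Keep the tests for comparing retention.
- State that the adjusted odds ratio is conditional, and report a standardised risk difference beside it.

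The cost is two terms in models already planned, a rule for occasional missing baseline values, and an odds ratio that is conditional and so not directly comparable with an unadjusted one. No new data collection is needed.

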### Interventions

#### Orientation and intervention sessions

Participants attend a 60-minute orientation before the start of the clinic sessions. They learn the background, purpose, format, and procedures of the study; provide informed consent; complete baseline measures; learn about TNP therapy and receive their first patch (the remainder of the patches are provided throughout active treatment); and provide breath carbon monoxide (CO) and saliva samples for cotinine analysis. We also cover smoking and health, self-motivation, and goal setting. In the CS-CBT condition, we explain that the group is framed within a cultural context, designed to emphasize African American race/ethnicity and cultural issues.

In accordance with previous research (Webb et al. 2010;Brandon et al. 1995) participants in both conditions are asked to reduce their smoking by one-half on the day before the first clinic session and to abstain completely from smoking on the first day of actual group treatment (session 1). They are also instructed to begin patch use on the morning of the first day of treatment (session 1; the target quit day) with the patch provided at orientation. This aspect of the protocol is unique from other cessation approaches that set the quit day several weeks post beginning the intervention. However, this evidence-based protocol has been successful in previous studies [e.g., Webb et al. 2010; Brandon et al. 1995 and is also the format we use in our ongoing cessation clinic. Participants who do not quit on the target day are encouraged to make a quit attempt by the third treatment session.

Participants in both conditions meet eight times over four consecutive weeks. Four sessions occur during week 1, two during week 2, and one weekly booster session during weeks 3 and 4. Depending on group size, the duration of sessions is 90–120 minutes in both conditions. We anticipate 8–16 participants per group. Co-therapy pairs of masters or bachelor’s level interventionists are trained to conduct sessions for one condition (CS-CBT or control) and supervised by the principal investigator (PI). Groups are held in a laboratory-based clinic. Incentives include $40 at session 1, $20 at session 5, $50 at session 8, $50 at the 3-month assessment, $70 at the 6-month assessment, and $70 at the 12-month assessment. Participants also receive $5 per session for transportation/parking and light refreshments at each session.

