#### Training and intervention fidelity

The interventionists are trained by the PI. Training includes relevant readings (smoking, cessation and relapse prevention, cognitive behavioral therapy, motivational interviewing), observation of two therapy groups, minimal contributions in the role of therapist, and finally, fully conducting sessions with weekly PI supervision. Detailed intervention manuals are followed closely and participants receive a daily agenda. Interventionists do not cross over to prevent contamination. Most sessions are audio recorded and will be coded using a 10-item scale for adherence [see Webb et al. 2010 by two independent evaluators. Codes will be transformed into percentages indicating the degree of protocol adherence.

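### The per-assessment logistic regressions are specified without the therapy-group adjustment that the plan gives to its mixed models, so their intervals are too narrow if outcomes within a group are positively correlated

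*Protocol article*

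**What the plan says.** Two consecutive sentences under Statistical analyses describe two analyses of the arm effect on abstinence.

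- The first: "Within-time logistic regressions will determine the odds of abstinence at each assessment, comparing CS-CBT to control". It mentions no therapy-group term and no clustered variance.
- The second introduces GLMMs for cessation over time, "including main effects and interactions, and accounting for nesting within groups".

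The same section adds: "Alpha will be set to .05, and adjusted for multiple comparisons". It does not name the adjustment method, and it does not say which of the two analyses is confirmatory.

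On delivery, the Randomization section makes the individual the unit of allocation, at 1:1. Treatment is then given as eight shared sessions. The section on orientation and intervention sessions states: "We anticipate 8–16 participants per group" (the Randomization section gives 8–12 enrolled). Each co-therapy pair is trained for one condition, and under Training and intervention fidelity: "Interventionists do not cross over to prevent contamination".

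**The concern.** Members of one therapy group share sessions, peers and therapists. The Background names social support as part of what group CBT provides, and Table 1 lists a buddy system in the culturally specific arm. Quit outcomes within a group may therefore be correlated. Individual randomization does not remove this, because the correlation arises after allocation, and both therapy groups and therapists are nested in arm.

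An ordinary logistic regression assumes independent participants. With positive within-group correlation it understates the standard error of the arm effect. The regressions in question give the arm odds ratio for the primary outcome, 7-day point prevalence abstinence, at every assessment. The authors evidently recognise the nesting but attach the adjustment to one model only. The same arm comparison could then receive two answers with different error rates, with no statement of which one counts.

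**Working it through.** **The plan's own figure.** The only sample-size statement is "65 participants per group will yield power = .80% with a two-sided significance level of 5" (percent), based on "four assessments, with a within-subjects correlation of .60". The article cites its formula without printing it. I assumed the usual repeated-measures formula for two proportions:

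n per arm = [1.960·√(2p̄q̄) + 0.842·√(p₁q₁ + p₂q₂)]² / d² × (1 + (k − 1)ρ)/k

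With k = 4 and ρ = .60 the last factor is (1 + 3 × .60)/4 = 0.70.

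- End of counseling, 75% against 51% (the article: "51% of participants who received standard CBT reported 7-day ppa at the EOC"): 62.3 × 0.70 = 43.6, so 44 per arm.
- 12 months, 30% against 14%: 104.0 × 0.70 = 72.8, so 73 per arm.

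The stated 65 lies between these. It is neither confirmed nor refuted, because the rates that entered the formula are not fully given. What matters here is that the .60 is correlation between repeated measures on one person. It is not correlation between members of a therapy group, so it cannot serve as the ICC.

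**Inputs for the check**

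- N = 247 (Participants and recruitment).
- Group size m = 8 to 16 (Orientation and intervention sessions).
- Nominal two-sided level .05 (Statistical analyses), before multiplicity adjustment.
- ICC: not in the article. Assumed range 0 to .10.

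**Formulas**

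- Design effect: DE = 1 + (m − 1) × ICC.
- Factor by which the interval (log-odds scale) should be wider: √DE.
- True error of an unadjusted test: 2 × [1 − Φ(1.96/√DE)].
- Effective sample size: 247/DE.

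Worked example, m = 16 and ICC = .05: DE = 1 + 15 × .05 = 1.75; √DE = 1.323; 1.96/1.323 = 1.48; true error = .138; effective N = 247/1.75 = 141.

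| m | ICC | DE | √DE | True error at nominal .05 | Effective N |
|---|---|---|---|---|---|
| any | 0 | 1.00 | 1.00 | .050 | 247 |
| 8 | .01 | 1.07 | 1.03 | .058 | 231 |
| 8 | .02 | 1.14 | 1.07 | .066 | 217 |
| 8 | .05 | 1.35 | 1.16 | .092 | 183 |
| 8 | .10 | 1.70 | 1.30 | .133 | 145 |
| 12 | .01 | 1.11 | 1.05 | .063 | 223 |
| 12 | .02 | 1.22 | 1.10 | .076 | 202 |
| 12 | .05 | 1.55 | 1.25 | .115 | 159 |
| 12 | .10 | 2.10 | 1.45 | .176 | 118 |
| 16 | .01 | 1.15 | 1.07 | .068 | 215 |
| 16 | .02 | 1.30 | 1.14 | .086 | 190 |
| 16 | .05 | 1.75 | 1.32 | .138 | 141 |
| 16 | .10 | 2.50 | 1.58 | .215 | 99 |

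**Simulation check.** A beta-binomial simulation of the plain logistic Wald test under no arm effect (20,000 runs per setting, about 247 participants, 30% abstinent in both arms) gave .057 at m = 8, ICC .01; .118 at m = 12, ICC .05; and .218 at m = 16, ICC .10. At ICC 0 it gave about .05. The formula and the simulation agree.

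**With a multiplicity adjustment.** The article does not name the method. If it were Bonferroni over four assessments (my assumption; .0125 per test, critical value 2.498), the per-test error would be 2 × [1 − Φ(2.498/√DE)]: .016 at DE 1.07, .028 at DE 1.30, .059 at DE 1.75 and .114 at DE 2.50. Each exceeds its nominal .0125, but only the larger design effects push a single test above .05.

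**The case against.** The strongest reply is that this is a condensed article. It does not say that the within-time models ignore therapy group; it is silent, and the full plan may contain a group term or a clustered variance. That stands as a limit on the claim, which concerns the text as written. It does not dispose of the point, because the article does state how clustering is handled and places it in one of two adjacent model descriptions.

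Second, the hypotheses (main effects of intervention and of time, no interaction expected) match the terms of the GLMM, which already accounts for nesting. This also stands: the GLMM arm test is unaffected. But the article names neither analysis as confirmatory.

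Third, alpha is to be adjusted for multiple comparisons. The unadjusted error rates therefore describe tests at .05 and would be lower under an adjusted level. The adjustment does not repair a standard error that is too small, so the relative excess over the nominal level remains.

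Three stronger readings are tempting, and the documents do not support them.

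- A reader might infer that the error rate certainly exceeds 5%. That depends on an ICC the article does not give: at ICC 0 there is no excess, and at ICC .01 the error is about 6% to 7%.
- A reader might count about 25 groups (247/10) and conclude that the trial holds only 25 independent observations. That is the number of clusters, which governs degrees of freedom. It would be the effective sample size only at an ICC of 1.
- The 22% end of the range needs ICC .10 and every group at its maximum of 16.

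**Conclusion.** The point holds in conditional form. As written, the nesting adjustment covers the GLMMs and not the per-assessment logistic regressions, although delivery in groups by arm-specific therapists affects both equally. If the within-group ICC is positive, the odds ratios at the four assessments will have intervals that are too narrow, by a factor of 1.03 to 1.58 over the assumed range, and tests above their nominal level.

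The size rests on the assumed ICC of .01 to .10, equal group sizes between 8 and 16, all 247 participants analysed, and no multiplicity adjustment.

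This is a cheap improvement to the plan. It is not shown to be a required correction, because the ICC is unknown, the article does not make the within-time regressions confirmatory, and a cluster-adjusted test of the arm effect is already planned.

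**What to change.** Either of two changes is enough.

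1. Take the arm odds ratio at each assessment from the planned GLMM, as arm-by-time contrasts with a random intercept for therapy group. The arm effect then comes from one model with one treatment of clustering.
2. Keep the within-time regressions, but fit each with a therapy-group random effect, or with a cluster-robust or GEE variance. Use a small-sample correction and degrees of freedom based on the number of groups, which is about 15 (247/16) to 31 (247/8) in total, or roughly 8 to 15 per arm.

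It would also help to state which analysis is confirmatory. A term for co-therapy pair should be left out unless there are several pairs per arm: pairs are nested in arm and their number is not given, so with few pairs the term is weakly identified, and with one pair per arm it cannot be separated from treatment.

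The cost is a change of wording and somewhat wider confidence intervals at each assessment. No change to design, recruitment or data collection is needed beyond recording each participant's therapy group.
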